### **13.9 Data Handling and Record Keeping**

The quality and retention of data that is collected as part of this trial is under the responsibility of the Chief Investigator, [name].

All trial data will be retained in accordance with the latest Directive on GCP (2005/28/EC) and local policy. Data will be handled, computerised and stored in accordance with the Data Protection Act 1998. Patients will be identified by a unique trial number. Data will be recorded by authorised site staff on electronic Case Report Forms (eCRFs) and stored on a secure validated MACRO database system managed by Newcastle Clinical Trials Unit. Caldicott approval will be sought at The Newcastle upon Tyne NHS Foundation Trust site to enable the collection of personal identifiable information for purposes of trial administration (including arranging patient assessments) and maintaining accurate screening records.

## **14. Statistical Considerations**

### **14.1 Statistical Definitions and Analysis**

All statistical analysis will follow a trial-specific predetermined statistical analysis plan (SAP), written and signed off prior to any statistical analysis of the trial data (excepting recruitment) and stored in the TMF.

#### **2.1.1 Cohort 1**

All patients will contribute to the analysis based on the total number recruited.

The primary outcome measure is the number of patients with severe or very severe treated skin site reactions as determined by modified Draize score (See Appendix A)

Patient perception of treatment is a secondary outcome measure as measured by the patient treatment questionnaire (See appendix B). Positive patient perception will be reported descriptively as a proportion of the number of patients recruited.

Statistical analysis for all outcome measures will be exploratory based on descriptive data. Continuous measurements (including QoL measures) will be summarised and reported as medians and ranges (inter-quartile ranges). Categorical data (including proportions of patients with positive patient perception and with adverse events) will be summarised and reported as percentages and confidence intervals (95%).

QoL tools (EQ5D, DLQ) will be scored according to scoring manuals and actual scores will be reported descriptively.

#### **2.1.2 Cohort 2**

All tumours will contribute to the analysis based on the total number randomised (intention to treat population). A secondary analysis will be reported based on the number of tumours which have been treated for 12 weeks (per protocol population).

The primary outcome measure is the number of tumours responding to treatment by 12 weeks reported as a proportion of the number of tumours randomised in the actively and placebo groups separately.

According to WHO-RECIST criteria, a reduction in 30% volume would be sufficient to classify a 'response' to treatment in oncology. In this trial we will use this criteria as a bench mark when determining a response in this patient population. As such one of the outcomes will be to consider and confirm a definition of 'response' to treatment in this group of patients. Tumour volume will be measured on 8 - 10 predetermined identified tumours in each patient prior to randomisation (baseline) and measured again on the same tumours at 4 and 12 weeks. The change in volume for each tumour will be recorded and classified as either having a response to treatment or not.

As an early phase trial, statistical analysis will be exploratory (not based on hypothesis testing) and will be based on descriptive data presented by treatment group. Continuous measurements (including change in tumour volume from baseline) will be summarised and reported as medians and ranges (inter-quartile ranges). Categorical data (including proportions of tumours with adverse events and outcomes from the Pain Assessment Forms) will be summarised and reported as percentages and confidence intervals (95%). Since multiple tumours are sited in individual patients, a secondary analysis based on a multi-level

modelling approach will be undertaken to investigate the relationship between any change in volume and randomised treatment accounting for the multi-level nature of the tumour measurements.

QoL tools (EQ5D, DLQ) will be scored according to scoring manuals and actual scores will be reported descriptively.

## **14.2 Number of Patients**

### **Cohort 1**

It is anticipated that there will be low numbers of treatment related adverse events in Cohort 1 and it is therefore both feasible and pragmatic to recruit 8 patients. It will be acceptable to move to cohort 2 as long as any unexpected treatment related adverse events are experienced in no more than 3 patients.

### **Cohort 2**

It is anticipated that 75 tumours could be measured in each treatment arm (150 tumours in total). Tumours receiving placebo treatment are not expected to respond to treatment, set to be very small at 5% ( $p_0$ ). This is the first exploratory trial and as such the design parameters are provided as an exemplar of the size of errors that may be anticipated with these patient numbers.

Using Fleming A'Herns early phase methodology (Fleming 1982, Ahern, 2001) any response on the experimental treatment  $<5\%$  ( $p_0$ ) would not indicate a treatment worthy of further investigation. 75 tumours recruited in the experimental arm would provide evidence of a minimum level of efficacy of approximately 15% ( $p_1$ ), indicating that a level of efficacy of  $>15\%$  would warrant further investigation, with associated error levels of 3.4% type I error ( $\alpha$ ) and 10.8% type II error ( $\beta$ ). This level of efficacy seems clinically plausible and relevant given that there is no current treatment in use for these patients.

The justification to investigate CT327 further is based on observing a minimum number of responses, referred to as the critical number (specified in the Statistical Analysis Plan). The trial will recruit an equal number of placebo-treated tumours to provide an unbiased benchmark.

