## 7.2 Cohort 2 summary

This is a phase 2a randomised, double-blind, single site, placebo controlled trial to investigate if CYLD defective tumours respond to CT327.

150 tumours will be needed to complete the trial, and recruitment will continue until we have the 12 week assessment for 150 tumours. We anticipate 15-20 patients may need to be recruited to the trial to achieve this.

Patients will typically have 8 or 10 eligible tumours each (see section 9.3 for cohort 2 inclusion criteria below).

Patients will be allocated both active and placebo treatments to be applied randomly to tumours on their left or right side (Group1: L=active; R=placebo, Group 2: L=placebo; R=active).

Four or five tumours on each side will be identified at baseline for measurements during the 12-week treatment period.

Photographs will be taken and the tumours numbered clearly and offered to the patients, who can refer to the tumour maps. They will be shown how to apply treatments using disposable finger tip applicators to prevent crossover and given a detailed instruction sheet for reference.

Volume measurements will be taken at baseline, week 4 and 12 at scheduled visits. All tumours will be assessed for tumour volume using the Life-Viz stereoscopic imaging system by a blinded assessor (Skvara, Kalthoff *et al.* 2011).

Patients will record application of treatment in a patient diary (See Appendix C).

Patients will also record if any of the selected tumours have any associated pain, this will be captured using the Patient Pain Assessment Form, which will be completed at baseline and repeated at 4 and 12 weeks.

After 12 weeks one tumour that is treated with active treatment and one tumour that has been treated with placebo will be biopsied to assess histological and immunohistochemical changes.

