## **11. Randomisation (cohort 2 only)**

A member of the trial team (as outlined in the delegation log) will re-check and confirm eligibility prior to randomisation. Eligibility can be confirmed by using information obtained from patient's notes and directly from the trial participants.

Randomisation will be at the per patient level randomising active and placebo treatments to left or right sided application. There will be no stratification at randomisation in this small early phase trial.

The statistics team will be responsible for preparing the allocation lists which will be uploaded to a secure web-based system by the database manager.

Randomisation will be administered centrally by the Newcastle Clinical Trials Unit internet-accessed secure web-based system which provides ease of operation, with in-built validation/plausibility checks at time of data entry.

The PI at site or an individual with delegate authority will access the web based randomisation system. Patient screening ID and initials will be entered into the web-based system. Patients will be allocated both active and placebo treatments to be applied randomly to left or right tumours (e.g. Group1: L=active; R=placebo, Group 2: L=placebo; R=active, where the terms L and R refer to the patient's left and right side). Patients allocated to a specific group (e.g. Group1: L=active; R=placebo), will remain in this same group when prescriptions are dispensed at baseline and week 4. Specific training will be given at site initiation.

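### The 3.4% and 10.8% error rates in protocol 14.2 assume 75 independent tumours, but these are clustered 4–5 per patient-side in 15–20 patients; the errors should be restated over a range of within-patient correlation

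*Combined protocol and SAP*

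**What the plan says.** Protocol 14.2 (Cohort 2) takes a placebo response rate "set to be very small at 5"% as the uninteresting level. "Using Fleming A'Herns early phase methodology", it then says that "75 tumours recruited in the experimental arm would provide evidence of a minimum level of efficacy of approximately 15"%, "with associated error levels of 3.4% type I error" and "10.8% type II error". It qualifies this: "the design parameters are provided as an exemplar of the size of errors that may be anticipated with these patient numbers". No intracluster correlation, design effect or effective sample size appears.

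Protocol 7.2 expects 15–20 patients and says "Patients will typically have 8 or 10 eligible tumours each", four or five on each side. Protocol 11 states: "Randomisation will be at the per patient level randomising active and placebo treatments to left or right sided application". So each patient contributes a group of 4–5 active tumours.

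Protocol 14.3 says that no further investigation is warranted if responses fall below the critical number. SAP 8.4 bases the end-of-Phase-2a decision mainly on the response rate and that number, and refers to a separate document for its value. SAP 8.2.2.2 reports the response proportion per tumour with a 95% confidence interval and mentions no clustering. Protocol 14.1 and SAP 8.2.2.3 do recognise that tumours are nested in patients, but only in a secondary multilevel model of tumour volume.

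**The concern.** The Fleming–A'Hern calculation counts independent units. Tumours on one side of one patient share a germline mutation, skin, an ointment supply and the habits of the person applying it. If their responses correlate positively, the number of responders varies more than the binomial allows. The count then reaches the critical number too often when the true rate is 5%, and misses it too often when the true rate is 15%. Both errors are understated together. For illustration, two patients in whom all 4–5 active tumours respond supply 8–10 responses by themselves.

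The volume model does not repair this, because the decision uses the responder count. A reader who weighs the trial's conclusion by the printed error rates would trust it too much in both directions.

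The sentence on 15% efficacy is a separate difficulty. It presents the alternative used for power as a minimum that the trial would demonstrate.

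**Working it through.** **Inputs.** From protocol 14.2: 75 active tumours, null rate p0 = 5%, alternative p1 = 15%, stated errors 3.4% and 10.8%. From protocol 7.2: 15–20 patients, 4–5 active tumours each. The critical number r is in neither document and is inferred in step 1. The ICC is an assumption, taken from 0.05 to 0.3.

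**Step 1: reproduce the stated errors.** With X binomial on 75 independent tumours and a positive result at X ≥ r:

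- α = P(X ≥ r | 75, 0.05)
- β = P(X ≤ r − 1 | 75, 0.15)

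| r | α | β |
|---|---|---|
| 7 | 8.1% | 5.4% |
| 8 | 3.36% | 10.82% |
| 9 | 1.2% | 18.9% |

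Only r = 8 matches the printed pair, so the protocol's figures are correct for 75 independent units.

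**Step 2: allow for patients.** Let each patient's number of responding active tumours be beta-binomial with mean rate p and ICC ρ, that is, with parameters a = p(1 − ρ)/ρ and b = (1 − p)(1 − ρ)/ρ. The distribution of the total is the exact convolution over patients. Two layouts keep the total at 75: 15 patients with 5 tumours each, and 19 patients (18 with 4 and one with 3, so 72 + 3). The rule stays at r = 8.

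The effective sample size is 75 / [1 + (m − 1)ρ]. In the first layout m = 5. In the second m = (18 × 16 + 9)/75 = 3.96. For example, at ρ = 0.2 the first layout gives 75/1.8 = 41.7.

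| Assumed ICC | 15 patients: α / β | Effective n | 19 patients: α / β | Effective n |
|---|---|---|---|---|
| 0 | 3.4% / 10.8% | 75 | 3.4% / 10.8% | 75 |
| 0.05 | 4.8% / 13.1% | 62.5 | 4.5% / 12.5% | 65.3 |
| 0.1 | 6.1% / 15.2% | 53.6 | 5.5% / 14.1% | 57.9 |
| 0.2 | 8.4% / 18.7% | 41.7 | 7.3% / 17.0% | 47.1 |
| 0.3 | 10.3% / 21.6% | 34.1 | 8.8% / 19.4% | 39.7 |

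**Step 3: check the model.** A logit-normal patient effect in place of the beta distribution agrees in direction and size. With a standard deviation of 1.5 and 15 patients with 5 tumours, α is 7.0% and β is 19.4%. That standard deviation corresponds to an ICC of about 0.14 at the 5% rate and 0.22 at the 15% rate.

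**Step 4: the 15% sentence.** The inferred boundary is 8/75 = 10.7%. Its exact 95% confidence interval, ignoring clustering, is 4.7% to 19.9%. Reaching the boundary therefore does not show a response rate of at least 15%. Under independence, 15% is the rate at which the design has power 100% − 10.8% = 89.2%.

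**The case against.** The strongest reply is that the protocol never claims strict error control. Section 14.2 calls the parameters an exemplar, section 14.1 calls the analysis exploratory without hypothesis testing, and SAP 8.4 makes the critical number the predominant basis for the decision, not the sole one. SAP 8.4 also leaves room to pursue a treatment that misses the boundary and takes the conclusions to the DMC. Placebo tumours on the other side of the same patients would reveal shrinkage unrelated to the drug. These points stand, and they lower the severity. They do not dispose of the concern: section 14.2 offers the rates as those to be anticipated with these patient numbers, the decision is still tied to the critical number, and the placebo count does not enter that rule.

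A reader might infer four stronger things that the documents do not support:

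- **That the arithmetic is wrong.** It is right; the independence assumption is unstated.
- **That the design cannot have the stated errors.** At an ICC of 0 they are exact, and at 0.05 the type I error stays below 5%. The inflation at the null rate also needs a shared cause that operates without a drug effect. Adherence to an ineffective ointment would not supply one.
- **That the critical number must rise to 9.** This presumes a 5% ceiling on type I error that neither document sets. With 15 patients and an ICC of 0.2, a critical number of 9 gives 4.8% and 26.8%. At an ICC of 0.3 it gives a type I error of 6.4%; a critical number of 10 gives 3.9%, with a type II error of 37.7%. That is a trade-off, not a correction.
- **That reaching 8/75 excludes 5%.** The two-sided interval in step 4 contains 5%, and clustering would widen it.

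**Conclusion.** The point holds as a should-fix. The printed errors are right only if tumours within a patient respond independently. The plan does not state that condition, and its own multilevel model gives reason to doubt it. Over the assumed ICC range of 0.05 to 0.3, the type I error is about 1.3 to 3.0 times the stated figure (4.5/3.4 to 10.3/3.4), and the type II error about 1.2 to 2.0 times (12.5/10.8 to 21.6/10.8).

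This rests on four assumptions: a positive ICC that the documents do not supply, the same ICC at both response rates, a critical number of 8 inferred from the stated errors, and 15 or 19 patients supplying exactly 75 active tumours. Any allowance for clustering in the separate critical-number document cannot be seen from here, but the rates printed in section 14.2 contain none. The 15% sentence needs rewording whatever the ICC.

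**What to change.** 1. In protocol 14.2, and in the critical-number document cited in SAP 8.4, state that 3.4% and 10.8% hold only if tumours within a patient are independent. Replace the single pair with the errors of the chosen critical number over a stated ICC range, such as 0 to 0.3, for the expected numbers of patients and tumours per side.
2. In SAP 8.2.2.2, calculate the confidence interval for the response rate with clustering by patient, and name the method.
3. In protocol 14.2, reword the efficacy sentence so that 15% is described as the rate at which the design has its stated power, not as a minimum shown by reaching the boundary.

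Whether to raise the critical number is for the sponsor to decide and is not part of this change.

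The cost is wording in two documents and the critical-number document, a short calculation, and less favourable stated errors. No extra patients are needed.

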## **14.3 Decision Criteria**

### **Cohort 1**

We anticipate recruiting 8 patients to cohort 1. It will be acceptable to move to cohort 2 as long as any unexpected treatment related adverse events are experienced in no more than 3 patients.

### **Cohort 2**

The Fleming A'Hern design would indicate no further investigation is warranted if the observed number of clinical responses is less than the critical number (as specified in the Statistical Analysis Plan).

## **15. Compliance and withdrawal**

### **15.1 Assessment of compliance**

Where feasible, trial visits will coincide with routine clinical follow-up, to enhance the likelihood of good compliance. Visit windows of +/- 3 days should ensure visit attendance; non-attendance for trial visits will prompt follow-up by telephone.

Compliance with trial medication will be assessed by checking the patient diaries and weighing and recording the returned jar after each treatment visit and at the final visit. Trial drug accountability will be assessed and documented by local pharmacy. The clinical team will also perform a quick review of any returned trial medication at each trial visit to identify any obvious compliance concerns and address these immediately with the participant.

### **15.2 Withdrawal of participants**

Trial drug must be discontinued if:

- The participant decides they no longer wish to continue
- Cessation of trial drug is recommended by the investigator
- Pregnancy
- Any significant medical condition (in the judgement of the site investigator)
- Localised reactions:

Any patient reporting treatment site reactions will be assessed in the clinic. A modified Draize score of 4 or above would result in discontinuation of the drug. In the event of such an adverse reaction, blinding may need to be broken to determine if the reaction is related to the application of the trial drug to the treated site. Once the blind is broken, the trial drug will need to be discontinued if it is found to be responsible for the adverse event.

- Systemic reactions:

Any other reported side effects/adverse events that the patient experiences during the trial will be assessed by the chief investigator. If clinically appropriate, the patient will be reviewed in clinic and a decision made regarding discontinuing the trial drug if it is feasible that this is related to the trial drug.

Participants have the right to completely withdraw from the trial at any time for any reason, and without giving a reason. The investigator also has the right to withdraw patients from the trial drug in the event of inter-current illness, adverse events, serious adverse events, suspected unexpected serious adverse reactions, protocol violations, cure, administrative reasons or other reasons. It is understood by all concerned that an excessive rate of withdrawals can render the trial uninterpretable; therefore, unnecessary withdrawal of patients should be avoided. Should a patient decide to withdraw from the trial, all efforts will be made to report the reason for withdrawal as thoroughly as possible. Should a patient withdraw from trial drug only, efforts will be made to continue to obtain follow-up data, with the permission of the patient.

Participants who wish to withdraw from trial medication will be asked to confirm whether they are still willing to provide the following.

- 'end of trial data' as per visit 3 (4 weeks) in cohort 1 or visit 4 (12 weeks) in cohort 2, at the point of withdrawal

- If participants agree to the above, they will be asked to complete a confirmation of withdrawal form to document their decision.

In cohort 1, participants who withdraw from trial drug prior to visit 3 will still be followed up and included in analysis, if they are happy to do so, but additional participants may be recruited provided withdrawal is not related to safety issues.

In cohort 2, participants who withdraw from trial drug will still be followed up and included in analysis, if they are happy to do so, but additional participants may be recruited and randomised as not to affect the recruitment target of 150 tumours and provided withdrawal is not related to safety issues.

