## **12. Trial Blinding (Cohort 2 only)**

Patients and investigators will be blinded to the treatment allocation. Those responsible for tumour volume measurements, histology assessments and molecular analysis will also be blinded to treatment allocation. The Trials Management Group including Trial Manager will be blind to the treatment allocation. The trial statistician may provide confidential unblinded data to the closed session of the external independent data monitoring committee (excluding members of the Trials Management Group).

Following the unlikely event of a code break, patients' will continue to be followed up if they agree to do so. If the unblinding reveals that the cause was the placebo ointment, patients will be offered the continuation of the trial medication as per the randomisation if they wish. The analysis of the trial will reflect the unblinding, data both including and excluding the unblinded participants will be analysed to avoid bias.

Code breaks will not be routinely performed for all participants who complete trial treatment but all patients may be informed of their allocations once the trial analysis is complete on request and the data released to the chief investigator.

At the final visit, the integrity of the blind will be assessed by asking the participants: Which side was receiving active treatment? Why do you think this?" on the patient treatment questionnaire. The treatment assessor will be asked to record their answer on a separate CRF and prior to asking the participant to avoid bias.

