#### **Causality:**

The assignment of the causality should be made by the investigator responsible for the care of the participant using the definitions in the table below. All adverse events judged as having a reasonable suspected causal relationship to the IMP(s) (i.e. definitely, probably or possibly related) are considered to be adverse reactions. If any doubt about the causality exists, the Chief Investigator should be informed. In the case of discrepant views on causality between the investigator and others, all parties will discuss the case. In the event that no agreement is made, the MHRA, main REC and other bodies will be informed of both points of view.

| Relationship   | Description                                                                                                                                                                                                                                                                                                         |
|----------------|---------------------------------------------------------------------------------------------------------------------------------------------------------------------------------------------------------------------------------------------------------------------------------------------------------------------|
| Unrelated      | There is no evidence of any causal relationship                                                                                                                                                                                                                                                                     |
| Unlikely       | There is little evidence to suggest there is a causal relationship (e.g. the event did not occur within a reasonable time after administration of the trial medication). There is another reasonable explanation for the event (e.g. the participant’s clinical condition, other concomitant treatment).            |
| Possible       | There is some evidence to suggest a causal relationship (e.g. because the event occurs within a reasonable time after administration of the trial medication). However, the influence of other factors may have contributed to the event (e.g. the participant’s clinical condition, other concomitant treatments). |

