## **7. SAFETY ANALYSIS**

Most adverse events (AE) and adverse drug reactions that occur in this trial, whether they are serious or not, will be expected treatment-related toxicities due to the drugs used in this trial. For a full list of expected undesirable effects of CT327, please refer to the Investigator Brochure.

AE's are recorded by the clinical staff directly to the database on a three-point scale of severity (mild, moderate or severe) and also by causality (relationship to treatment categorised on a six point scale), as described in the protocol.

The analysis sets are the Phase 1b treatment set and the Phase 2a treatment set.

Any adverse events/reactions from start of treatment and up to the time of tumour excision (Phase 1b) or 4 weeks after end of treatment (Phase 2a), will be categorised according to severity and causality and recorded on the database.

The number of patients (Phase 1b) and tumours (Phase 2a) reporting any AE will be reported clarifying those deemed to be treatment related (Appendix 2).

In Phase 2a, the number of tumours with at least one AE will be reported as a proportion of the total number of tumours. The number of tumours with at least one treatment-related AE, that is those described as definitely, probably or possibly related, will be reported as a proportion of the total number of tumours. The number of tumours with at least one 'moderate' or 'severe' treatment-related AE will be reported as a proportion of the total number of tumours.

The unique number of patients experiencing at least one 'moderate' or 'severe' treatment-related AE will be reported as a proportion of the treatment set.

Proportions will be presented as % (95% CI).

Descriptions of the adverse events may require listing in the text.

No significance testing will be carried out.

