## SAFETY ANALYSIS

### Adverse Events

| Tumours                                                                                                   | Active
N= | Placebo
N= | Total |
|------------------------------------------------------------------------------------------------------------------|----------------------|-----------------------|--------------|
| Any AE
Yes*
No                                                                        |                      |                       |              |
| * Severity
Mild
Moderate
Severe                                             |                      |                       |              |
| * Treatment related
Yes
Definitely
Probably
Possibly
No |                      |                       |              |

## Appendix 3

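### Cohort 2: causality can be graded after a code break made to decide relatedness, yet related events are tabulated by arm, so the grade should be recorded before the code is opened

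*Combined protocol and SAP*

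**What the plan says.** **Default blinding.** Protocol section 12: "Patients and investigators will be blinded to the treatment allocation". Under section 17.1, "The assignment of the causality should be made by the investigator responsible for the care of the participant". So the grade is normally given blind.

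**Exception.** Section 15.2 deals with localised reactions. It first states that "A modified Draize score of 4 or above would result in discontinuation of the drug". It then says that "blinding may need to be broken to determine if the reaction is related to the application of the trial drug to the treated site", and adds: "Once the blind is broken, the trial drug will need to be discontinued if it is found to be responsible for the adverse event". Section 12 covers what follows a code break and includes the condition "If the unblinding reveals that the cause was the placebo ointment". It also promises analyses with and without the unblinded participants.

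**Reporting.** SAP section 7 counts tumours with at least one related event, "that is those described as definitely, probably or possibly related". The adverse event shell in SAP Appendix 2 has a "Treatment related" block under Active and Placebo columns, alongside rows for any event and for severity. Proportions carry 95% confidence intervals and nothing is tested.

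**Silence.** No section says whether causality is recorded before or after the code is opened, or which grade is tabulated if it changes.

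**The concern.** Opening the code tells the investigator which ointment was on which side. It does not tell them what caused the reaction. Sections 15.2 and 12 nevertheless treat the first as an answer to the second. If the grade on the adverse event form is set or revised after the code is known, relatedness is partly a function of the arm, and it is then compared between arms.

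The likely direction is clear. A reaction on the CT327 side is easily called related once the code is known. The same reaction on the vehicle side may be called unrelated to trial drug, although section 10.5 gives both ointments the same base and the active one differs only by containing CT327. A vehicle effect that is equal on both sides could then look like an excess on CT327.

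The analysis with and without unblinded participants does not repair this. Including them keeps a grade given with the allocation known, and excluding them removes the patients with the reactions of interest. SAP section 7 does not mention that analysis.

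**Working it through.** **The plan's own figures.** The documents give no rate for severe site reactions or for code breaks, so there is no stated figure on this point to reproduce. The only design figures for cohort 2 are those in protocol section 14.2: 75 tumours per arm, with response rates of 5% and 15%. An exact binomial rule of at least 8 responses in 75 gives a type I error of 3.4% and a type II error of 10.8%, as stated. This confirms 75 as the denominator and has no other bearing here.

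**Inputs from the documents**
- 75 tumours per arm, 150 in total (section 14.2).
- Four or five tumours on each side (section 7.2), with sides randomised within patient (section 11). One code break therefore discloses both sides: 8/150 = 5.3% to 10/150 = 6.7% of all tumours.
- Application site reactions in earlier studies: 3%, any severity (section 17.2).
- 15 to 20 patients (section 7.2).

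**Step 1: effect of one attribution decision on one arm**
- One tumour reacts: 1/75 = 1.3 points.
- A whole side reacts: 4/75 = 5.3 to 5/75 = 6.7 points. This is the ceiling for one patient.

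**Step 2: how often it might arise.** If the 3% applied per patient, 0.03 × 15 = 0.45 to 0.03 × 20 = 0.60 patients would have a site reaction of any severity. Those scoring 4 or above and actually unblinded would be fewer.

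**Step 3: expected bias with no true difference (illustration; all rates assumed).** Let r be the reaction rate per tumour in both arms, q the chance that a reaction is graded related while blinded, and u the share of reactions unblinded before the grade is set. As the extreme case, suppose that after unblinding the active side is always graded related and the placebo side never.
- Active: r × [(1 − u) × q + u]
- Placebo: r × (1 − u) × q
- Spurious difference: r × u

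With r = 3%, q = 0.5 and 75 tumours per arm:

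| u | Related, active | Related, placebo | Difference (points) |
|---|---|---|---|
| 0 | 1.12 | 1.12 | 0 |
| 0.25 | 1.41 | 0.84 | 0.75 |
| 0.5 | 1.69 | 0.56 | 1.5 |
| 1 | 2.25 | 0 | 3.0 |

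For u from 0.25 to 1, the difference runs from 0.25 to 1.0 points at r = 1%, and from 1.5 to 6.0 points at r = 6%. The all-causality count stays at 75 × 0.03 = 2.25 per arm whatever the value of u.

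**Step 4: relaxing the extreme case.** If an unblinded placebo-side reaction is still graded related with chance s, the difference becomes r × u × (1 − s). At r = 3%, u = 0.5 and s = 0.5, that is 0.03 × 0.5 × 0.5 = 0.75 points. At s = 1 it is zero.

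**The case against.** Much of the case on the other side stands.

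- **The order is not stated.** Section 15.2 is about withdrawal, and the code break there serves a decision on continuing treatment. The causality categories in section 17.1 rest on timing and alternative explanations and do not mention allocation. A reader might infer that the grade on the form must follow the code. The documents do not say so. They only fail to prevent it.
- **Placebo-side reactions can be related.** In section 17.1, treatment includes comparative agents. Section 12 accepts placebo as a possible cause, and the Appendix 2 shell has related rows under Placebo. Against this, the causality paragraph refers to the IMP(s), section 10.1 names CT327 as the IMP, and section 15.2 speaks of trial drug. The wording therefore permits a related grade for vehicle but does not ensure it.
- **Other harm rows are intact.** A reader might take the related-event block as the only controlled evidence on harm. The any-event and severity rows by arm do not use causality. Section 17.3 mentions recording non-serious adverse reactions only, but section 17.4 and SAP section 7 cover all adverse events.
- **The severity scales differ.** A reader might equate Draize 4 or above with a moderate or severe adverse event. Appendix A grades erythema and papulation or infiltration, while section 17.1 grades disruption of daily life. The shell has no row for related events by severity.
- **Breaks should be few and traceable.** Section 15.2 is permissive, section 12 calls a code break unlikely, and section 10.4 requires its reason to be documented.

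None of this supplies a blinded grade for a reaction whose code has been opened. Nor does the absence of a test remove bias from an estimate reported with a confidence interval.

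**Conclusion.** The gap is real: a stated rule lets allocation inform an attribution that is then compared by arm, and nothing fixes the grade beforehand. The likely direction is against CT327. The size cannot be derived from the documents and is probably small: 1.3 points for a single tumour and 5.3 to 6.7 points at most for one whole side.

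A reader might go further and say that all severe reactions are affected, or picture 5/75 related on active against 0/75 on placebo. The first treats a ceiling as an estimate. The second needs every selected tumour on both sides of one patient to react and then opposite grades for identical reactions. Neither has support in the documents. The percentages in step 3 depend on assumed rates and on the extreme grading rule.

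**What to change.** **Protocol sections 17.1 and 17.4.** Require severity and causality to be recorded and time-stamped for each side before any non-emergency code release, with causality judged against the ointment applied to that side, active or vehicle. Flag any grade first set or changed after unblinding.

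**SAP section 7 and Appendix 2.** Base by-arm related counts on the grade recorded before unblinding. List later changes separately. Name the all-causality rows by arm as the main harm comparison.

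**Cost.** A sentence or two in each document and a time stamp on the adverse event form. The tabulated grade may differ from a later regrade made for regulatory reporting, hence the listing.

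**To be reconciled by the sponsor.** Section 15.2 links a Draize score of 4 or above to discontinuation, then makes discontinuation after a code break depend on what is found responsible. Section 12 describes an offer to continue where placebo was the cause. These passages need to agree with each other. No clinical rule is proposed here, and emergency unblinding is untouched.
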